# Efficacy and safety of electro-acupuncture treatment in improving the consciousness of patients with traumatic brain injury: study protocol for a randomized controlled trial

**DOI:** 10.1186/s13063-018-2687-3

**Published:** 2018-05-29

**Keywords:** Electro-acupuncture, Traumatic brain injury, Consciousness, Mismatch, Negativity

## Abstract

**Background:**

Traumatic brain injury (TBI) has become a leading cause of death among young people worldwide. Survivors may live with a long-term TBI-related disability or even develop a disorder of consciousness resulting in poor life quality and shortened life expectancy. Thus far, very few approaches have been found to be effective in the consciousness recovery of these patients. Acupuncture has long been used in the treatment of neurological disorders in China. However, its efficacy and safety in consciousness recovery remain to be proved.

**Methods:**

Here, we present a study design and protocol of a randomized, blinded, controlled study to evaluate the efficacy and safety of electro-acupuncture in the consciousness recovery of patients with TBI. A total of 150 patients with initial Glasgow coma scale score of less than 8 points will be recruited in the trial and randomized into acupuncture or control groups. Patients in the control group will receive routine pharmacological treatment alone while patients in the acupuncture group will receive electro-acupuncture treatment for 10 days in addition to routine treatment. The efficacy will be assessed with the changes in Glasgow coma scale score and mismatch negativity of event-related brain potentials before and after treatment. Moreover, Glasgow outcome scale and Barthel index of activities of daily living will be compared between the two groups at 3 months after treatment. The secondary outcome measures are the length of stay in ICU and hospital, expenses in ICU and hospital, as well as the incidence of coma-related complications. The safety of electro-acupuncture will be assessed by monitoring the incidence of adverse events and changes in vital signs during the study.

**Discussion:**

Results from this trial will significantly add to the current body of evidence on the role of electro-acupuncture in the consciousness recovery of patients with severe TBI. In addition, a more convenient and consistent electro-acupuncture method can be set up for clinical practice. If found to be effective and safe, electro-acupuncture will be a valuable complementary option for comatose patients with TBI.

**Trial registration:**

Chinese Clinical Trial Registry: ChiCTR-INR-17011674. Registered on 16 June 2016.

**Electronic supplementary material:**

The online version of this article (10.1186/s13063-018-2687-3) contains supplementary material, which is available to authorized users.

## Background

Traumatic brain injury (TBI) is a major cause of mortality and morbidity in young people [1]. Despite the continuous advances in neurosurgery, numerous survivors suffer from TBI-related disabilities. It is estimated that 5.2 million and 7.3 million people in the USA and in the European Union, respectively, have disabilities due to TBI [2, 3]. Given the rapid development of urban construction and transportation, the incidence of TBI in China has increased dramatically in recent years, with the current mortality rate within the range of 2.7% to 21.8% [4]. Due to the limited healthcare and rehabilitation sources, TBI survivors depend mainly on their families for their treatment, especially those who fail to recover consciousness. Therefore, the TBI-related disability of survivors has become a critical public health issue in China.

Neurocognitive deficits are common in patients with severe TBI. Patients who fail to fully recover consciousness may enter a disorder of consciousness (DOC) such as coma, a vegetative state, or a minimally conscious state [5]. With the development of diagnostic tools such as functional magnetic resonance and electroencephalography, clinicians are able to detect DOC in patients with severe TBI and commence early intervention [6, 7]. Current therapeutic strategies for DOC include behavioral, pharmacological, and neurostimulatory approaches, among which the latter two have been intensively studied. For example, amantadine and other dopaminergic agents have shown beneficial effects in promoting recovery after TBI, but warrant further systemic investigation [8–10]. As a potential restorative treatment for DOC, neurostimulation has attracted increasing interest. A study of thalamic deep brain stimulation demonstrated a remarkable behavioral recovery in patients with TBI [11]. Non-invasive forms of neurostimulation, such as transcranial magnetic stimulation and transcranial direct current stimulation, have shown some short-term effects on behavioral improvement, but need further study [12–14].

Acupuncture therapy is an important component of traditional Chinese medicine and has long been used in China to promote the neurological functions in patients with stroke and hemiplegia [15]. Although numerous studies have been conducted to evaluate the effects of acupuncture, results from these randomized controlled trials are controversial due to problems concerning the study design, including small sample size, high drop-out rate, lack of proper control, and randomization [16].

Herein, we present a study design and protocol of a randomized, blinded, controlled study to evaluate the efficacy and safety of electro-acupuncture in improving the consciousness level in patients with TBI. This study aims to provide high-quality evidence for the application of acupuncture in the management of comatose patients as well as to establish a standard acupuncture procedure for clinical practice.

## Methods

### Design and setting

This is a single-center, randomized controlled trial. This study has been approved by the Ethical and Biomedical Research Committee of West-China Hospital, Sichuan University. It is registered on http://www.chictr.org.cn with registration number ChiCTR-INR-17011674.

The study will be conducted in the West-China Hospital of Sichuan University. The legal representative of each patient will be asked to sign an informed consent form. To avoid selective bias, all enrolled patients will be divided into two equal groups to receive either acupuncture plus routine treatment (acupuncture group) or routine treatment alone (control group) using the random scheme generated from SPSS software. The serial number will be sealed in a non-transparent envelope by the principal investigator and given to the researcher. Acupuncture will be performed by doctors from the Department of Traditional Chinese and Western Medicine. The efficacy and safety will be evaluated by doctors from the Department of Critical Care Medicine, Department of Neurosurgery and Department of Neurology, who will be blind to the allocation of the patients.

### Participants

A total of 150 patients with TBI being treated at West-China Hospital of Sichuan University will be enrolled in this study after the legal representative signs the informed consent. The inclusion, exclusion, and withdrawal criteria are described in Table 1.

**Table 1 Tab1:** Inclusion and exclusion criteria for electro-acupuncture in severe traumatic brain injury trial

Inclusion	Patients with severe traumatic brain injury admitted to ICU: • Initial GCS score less than 8 points on admission • Estimated ICU stay longer than 2 weeks • Normal consciousness level before brain injury, no primary disorders in cognitive or motor function • Aged from 18 to 75 years • Agree to participate in the study and sign the informed consent
Exclusion	Patients are excluded from the study if any of the following criteria apply: • Vital signs are not stable on admission, die within 24 h • Women with pregnancy • Legal representative or immediate family has no strong treatment intent, can withdraw from treatment within 1 week • Patients with multiple trauma associated with limb fracture or skin defect
Withdrawal	Patients will be withdrawn from the study if any of the following criteria applies: • Life-threatening complications • Secondary hydrocephalus • Uncontrolled intracranial infection • Re-operate due to varieties of causes • Massive cerebral infarction • Unable to follow-up

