### Outcome measures

The primary measurements for efficacy assessment will be changes in Glasgow Coma Scale (GCS) and MMN. Additionally, Glasgow Outcome Scale and Barthel Index of Activities of Daily Living at 3 months after the trauma will be compared between the two groups. Secondary measurements will be the length of stay in ICU and hospital, expenses in ICU and hospital, and the incidence of coma-related complications. Safety will be assessed by monitoring adverse events as well as changes in vital signs during the study (see Fig. 2 and Additional file 1: Standard Protocol Items: Recommendations for Interventional Trials (SPIRIT) Checklist).

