### Sample size calculation

The purpose of this study is to clarify the role of acupuncture in the consciousness recovery of patients with TBI. Therefore, GCS change will be used as an evaluation index. Changes in GCS before and after treatment in our pilot study were shown to be 2.27 ± 3.52 (*n* = 11) in the control group and 3.70 ± 2.16 (*n* = 12) in the acupuncture group. Sample size was calculated using the following formula:$$ n={\left[\frac{\left({Z}_{\alpha /2}+{Z}_{\beta}\right)\sigma }{\delta}\right]}^2\left(\frac{1}{Q_1}+\frac{1}{Q_2}\right) $$where *n* represents the number of samples required, *n* = *n*_1_ + *n*_2_, Q_1_ = *n*_1_/*n*, Q_2=_
*n*_2_/*n* with 80% power and significance level at 5% for a two-sided test. Thus, allowing for 10% of attrition, we will recruit 150 participants, with 75 in each group.

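### Table 1 withdraws randomised patients from the study for setbacks that mark a bad course; this can bias the efficacy comparisons, and the 10% attrition allowance is not justified against it

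*Protocol article*

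**What the plan says.** The Withdrawal row of Table 1 (Participants) opens with "Patients will be withdrawn from the study if any of the following criteria applies" and lists "Life-threatening complications • Secondary hydrocephalus • Uncontrolled intracranial infection • Re-operate due to varieties of causes • Massive cerebral infarction • Unable to follow-up". The patient leaves the study, not only the acupuncture, and no time window is given.

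Safety monitoring has a narrower rule: a severe adverse event stops the acupuncture, adverse events are recorded, and severe ones are reported within 48 h. It does not say that the patient leaves the study.

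Outcome measures lists change in GCS and MMN, Glasgow Outcome Scale and Barthel Index at 3 months, and, as a secondary measure, "the incidence of coma-related complications".

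Sample size calculation specifies a design "with 80% power and significance level at 5% for a two-sided test" and ends: "Thus, allowing for 10% of attrition, we will recruit 150 participants, with 75 in each group". The only related rate in the article is in the Background, for TBI in China generally: "with the current mortality rate within the range of 2.7% to 21.8"%.

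**The concern.** Five of the six criteria are clinical setbacks that can occur after randomisation, and a patient who has one is less likely to show a good GCS change or a good 3-month result. If such patients leave the study, the outcome itself helps to decide who is compared. An arm with more setbacks loses more of its poor results and appears to do better, which is the wrong direction for a trial that also has to assess safety. Follow-up for later complications ends as well. Finally, the 10% allowance has to cover these withdrawals on top of ordinary loss to follow-up.

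**Working it through.** **1. The two rules side by side.** Table 1 ends study participation; Safety monitoring ends only the acupuncture. A life-threatening complication could fall under both, with different consequences. Nothing shown says that a withdrawn patient is still assessed or analysed.

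**2. The plan's own sample size.** Inputs from the pilot: "2.27 ± 3.52 (*n* = 11) in the control group" and "3.70 ± 2.16 (*n* = 12) in the acupuncture group".
- Difference: 3.70 − 2.27 = 1.43.
- SD pooled by degrees of freedom: √[(10 × 3.52² + 11 × 2.16²)/21] = √[(123.90 + 51.32)/21] = 2.889.
- The article's formula with equal arms: n = [(1.960 + 0.842) × 2.889/1.43]² × 4 = 128.1, so 65 per arm. Dividing by 0.90 gives 73 per arm, 146 in total.
- With the root-mean-square SD of 2.920: 66 per arm, then 74, 148 in total.

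The stated 150 is therefore reproduced closely, and the arithmetic is sound if loss is 10%.

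**3. Power if loss is larger.** Two-sided 5% t-test (noncentral t), difference 1.43, SD 2.889, evaluable N = 150 × (1 − loss). The last column is the planned rank-sum test, approximated by multiplying N by 0.955. The loss rates are assumptions, except that 21.8% is the top of the Background mortality range.

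| Loss | Evaluable | t-test | Rank-sum |
|---|---|---|---|
| 10% | 135 | 0.81 | 0.80 |
| 13% | 130.5 | 0.80 | 0.78 |
| 21.8% | 117 | 0.76 | 0.74 |
| 30% | 105 | 0.71 | 0.69 |
| 40% | 90 | 0.64 | 0.62 |

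The t-test crosses 80% at about 13% loss, in line with 1 − 65/75 = 13.3%. With SD 2.920 the corresponding limit is 1 − 66/75 = 12%. To keep 65 evaluable per arm, the total would be 164 at 20% loss (65/0.80 = 81.25, so 82 per arm) and 186 at 30% (65/0.70 = 92.9, so 93 per arm).

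**4. Size of the bias when there is no true effect.** Suppose the worst share p of an arm on a prognostic score is withdrawn, and that score has correlation r with GCS change. Under normality the mean of those who remain is too high by r × SD × λ(p), where λ(p) = φ(z_p)/(1 − p), z_p is the p-quantile of the standard normal and φ its density. λ is 0.195, 0.274, 0.350 and 0.497 at p = 10%, 15%, 20% and 30%. With r = 0.7 (assumed), r × SD = 0.7 × 2.889 = 2.022.

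| Withdrawn, control v acupuncture | Spurious benefit (GCS points) | Share of 1.43 | Rank-sum false positives (simulated, 75 per arm) |
|---|---|---|---|
| equal (10%, 20% or 30%) | 0 | 0% | about 5% |
| 10% v 15% | 2.022 × 0.079 = 0.16 | 11% | about 6% |
| 10% v 20% | 2.022 × 0.155 = 0.31 | 22% | about 9–10% |
| 20% v 30% | 2.022 × 0.147 = 0.30 | 21% | about 9–10% |
| 10% v 30% | 2.022 × 0.302 = 0.61 | 43% | about 23–25% |

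The simulated mean differences agree to within about 0.02 points. The bias is proportional to r: it halves at r = 0.35. At r = 1 with SD 2.9, 10% v 20% gives 0.45 points. If acupuncture had the fewer withdrawals, the sign would reverse.

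**The case against.** Several stronger readings are tempting, and the document does not support them.

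- *A reader might infer that withdrawals cannot fit within 10%.* No rate is given for any listed event. The mortality range is for TBI generally, is not a withdrawal rate, and lies on both sides of 10%. Enrolment excludes patients with unstable vital signs, and inability to follow up is the ordinary attrition that such an allowance is meant to cover.
- *A reader might infer that 80% power is lost as soon as loss passes 10%.* On the t-test it holds to about 13%. Only the rank-sum approximation is already at 0.80 at 10% loss.
- *A reader might infer that randomisation is broken in any case.* A biased difference needs withdrawal, or the reasons for it, to differ between arms. Nothing in the document predicts an imbalance, although the safety objective means that balance cannot be assumed.
- *A reader might infer that harms vanish from the safety count, or that the criteria are themselves the secondary outcome.* The triggering event can still be recorded under Safety monitoring; what is lost is follow-up afterwards. The article does not list which complications count as coma-related.

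It can also be said that analysis sets belong in a statistical analysis plan, which is not shown. That is fair, and their absence is not criticised here. But the withdrawal rule is fixed in the protocol, and no later analysis set can recover assessments that were never made.

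**Conclusion.** The concern holds in this form: Table 1 fixes a mandatory, open-ended withdrawal from the study on post-randomisation signs of a bad course, and it does not agree with Safety monitoring, which stops only the acupuncture. Followed literally, the rule removes poor results from the efficacy comparisons. The bias runs from zero with equal withdrawal to about 0.6 GCS points at 10% against 30%. Those figures rest on assumed withdrawal rates, an assumed correlation of 0.7 and normality. The 10% allowance is unjustified rather than shown to be wrong: it has a margin to about 13% loss on the t-test, and at 21.8% loss power would be 0.76. The defect in the wording is certain; its size in this trial is not known. It warrants correction because it is avoidable and could make an arm with more harm look better on the primary outcome. Trial status says recruitment is ongoing, so the loss of data can still be prevented.

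**What to change.** Reword the Withdrawal row so that the five clinical events do not end study follow-up, and reconcile it with Safety monitoring. Whether acupuncture continues after such an event is a separate clinical decision, on which nothing is proposed here.

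Collect post-treatment GCS and MMN, and Glasgow Outcome Scale and Barthel Index at 3 months, in every randomised patient unless consent is withdrawn or the patient cannot be reached. Analyse patients as randomised, with deaths ranked worst in the rank-sum analyses already planned. Count the listed events as complications or adverse events, by arm. Base the attrition allowance on the expected true loss, and restate power or sample size if that exceeds about 13%.

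The cost is a change of wording, some continued follow-up effort at 3 months, and possibly a slightly less favourable power figure.

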### Procedure

Figure 1 shows the study procedure flowchart. Potential participants from the Department of Critical Care Medicine, Shangjin clinics, West-China Hospital of Sichuan University, will be enrolled according to the inclusion criteria and randomized into the acupuncture or control groups. In addition to routine treatment, patients in the acupuncture group will receive a 10-day electro-acupuncture treatment. Acupuncture will start 3 days after trauma if the patient’s situation is stable. Patients in the control group will receive routine treatment alone, involving the prescription of coma arousal and neuroprotective agents by the neurosurgeons. If the patient needs vasoconstrictor or hypothermia therapy due to an unstable intracranial situation, electro-acupuncture will be started 3 days after the end of such treatments.

**Fig. 1 Fig1:**
[figure not shown]
Flow chart of the study procedure

### Electro-acupuncture procedure

Patients in the acupuncture group will be treated at acupoints PC6 (Neiguan) and GV26 (Shuigou), as described in Table 2. The patient will be placed in a supine position. After disinfection of skin with 75% alcohol, the acupuncture needles (stainless steel, sterile and disposable, 30-guage in thickness, and 45 mm in length, Jiajian Medical Instrument Co. Std, Jiangsu, China) will be inserted into the respective acupoints. The needle will be inserted perpendicularly for PC6 at a depth of 20 mm. For GV26, the needle will be inserted towards the nose at a depth of 5–10 mm. The needle will be manipulated using twirling, lifting, thrusting, and mild reinforcing-reducing methods to promote Qi. Eye moisture or the presence of tears will be used as an indicator of Qi arrival since patients are not able to express their feelings. The electro-acupuncture apparatus electrodes will then be linked onto the needle handles of both sides of PC6. The electro-acupuncture apparatus will be set for disperse-dense waves at a frequency of 10/50 Hz and current of 1 mA. The needles will be retained for 60 min after electro-acupuncture for 30 min duration. Due to the specific location of GV26, only hand manipulation will be applied for 30 min.

**Table 2 Tab2:** Description of acupuncture points

Acupoints	Descriptions
PC6: Neiguan	Locations: 2 cun above the transverse crease of the wrist, between the tendons of m. Palmaris longus and m. flexor radialis Indications: cardiac pain, mental disorder, epilepsy, insomnia, vomiting, hiccup, febrile disease Insertion depth: 20 mm
GV26: Shuigou	Locations: at the junction of the upper and middle third of the philtrum Indications: mental disorders, epilepsy, hysteria, coma, aplexy-faint Insertion depth: 5–10 mm

### Electrophysiological methods

To assess the patients’ consciousness level, event-related potentials (ERP) will be recorded from scalp electrodes placed on sites CZ and FZ according to the international 10–20 system, using the nose as reference. Mismatch negativity (MMN) will be produced using a pitch change in a repetitive auditory sequence. ERP will be recorded before electro-acupuncture starts, after the 10-day acupuncture is completed, on the day when the patient is discharged from ICU, and on the day of hospital discharge. MMN will be recorded at the same time of day for each measurement.

### Outcome measures

The primary measurements for efficacy assessment will be changes in Glasgow Coma Scale (GCS) and MMN. Additionally, Glasgow Outcome Scale and Barthel Index of Activities of Daily Living at 3 months after the trauma will be compared between the two groups. Secondary measurements will be the length of stay in ICU and hospital, expenses in ICU and hospital, and the incidence of coma-related complications. Safety will be assessed by monitoring adverse events as well as changes in vital signs during the study (see Fig. 2 and Additional file 1: Standard Protocol Items: Recommendations for Interventional Trials (SPIRIT) Checklist).

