### Statistical analysis

SPSS 17.0 (IBM SPSS, Chicago, IL, USA) will be used to analyze the data. Quantitative data will be presented as mean ± SD. Single factor variance analysis will be used to compare the difference in heart rate, blood pressure, mean arterial pressure, respiratory rate, and saturation of pulse oxygen between the two groups. The χ^2^ test will be used to compare the incidence of complications and adverse events between groups. Measurement of neural function recovery, including GCS, Glasgow Outcome Scale, and activities of daily living, will be analyzed using rank sum-test. Longitudinal changes in MMN amplitude will be analyzed using a mixed model procedure. *P* values of less than 0.05 will be considered statistically significant.

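### GCS change and MMN change are both named primary, each tested at 0.05 with no rule on whether one or both must succeed, while the trial is sized on GCS change alone

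*Protocol article*

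**What the plan says.** All references are to the protocol article.

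- **Outcome measures** names two primaries: "The primary measurements for efficacy assessment will be changes in Glasgow Coma Scale (GCS) and MMN". It continues: "Additionally, Glasgow Outcome Scale and Barthel Index of Activities of Daily Living at 3 months after the trauma will be compared between the two groups". The secondary list follows and contains neither of those two scales: "Secondary measurements will be the length of stay in ICU and hospital, expenses in ICU and hospital, and the incidence of coma-related complications". The Methods part of the Abstract keeps the same order.
- **Statistical analysis** gives the primaries separate tests. For GCS: "Measurement of neural function recovery, including GCS, Glasgow Outcome Scale, and activities of daily living, will be analyzed using rank sum-test". MMN amplitude over time goes into a mixed model. One threshold covers everything: P "values of less than 0.05 will be considered statistically significant". No order of testing, division of alpha or adjustment is given.
- **Sample size calculation** uses one outcome: "Therefore, GCS change will be used as an evaluation index". It takes pilot changes of 2.27 ± 3.52 (control, n = 11) and 3.70 ± 2.16 (acupuncture, n = 12), 80% power, a two-sided 5% level and 10% attrition, and arrives at 150 patients, 75 per group.

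**The concern.** With two primary outcomes, the error rate and power of the primary conclusion depend on the rule that joins them, and the article gives no rule. Followed as written, a trial that is negative on GCS and positive on MMN could be reported as meeting a primary outcome at the 5% level. Its real chance of doing so under no effect would be higher than 5%. If instead both outcomes are required, the 80% planned for GCS is only an upper guide to the power of the trial, because the article gives no effect size, SD or power for MMN. The sample size section treats GCS as the outcome that decides the trial. The outcome section puts MMN beside it at equal rank.

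**Working it through.** **1. The plan's own figure.** The inputs are those of Sample size calculation: difference 3.70 − 2.27 = 1.43, equal groups (Q1 = Q2 = 0.5), z = 1.960 and 0.842. The common SD is not stated, so two usual choices are tried.

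- Root-mean-square SD: √[(3.52² + 2.16²)/2] = 2.920. Total n = 4 × [(1.960 + 0.842) × 2.920/1.43]² = 130.9, so 66 per arm. Then 66/0.9 = 73.3, so 74 per arm and 148 in total.
- Pooled SD weighted by degrees of freedom: √[(10 × 3.52² + 11 × 2.16²)/21] = 2.889. Total n = 128.1, so 65 per arm. Then 65/0.9 = 72.2, so 73 per arm and 146 in total.

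Both are within 3% of 150. The arithmetic is sound for one outcome, GCS change, at the full 5%.

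**2. If success on either primary is enough.** With independent tests the chance of at least one false positive is 1 − 0.95² = 9.75%. With correlated normal test statistics it is 1 − P(|Z1| < 1.96 and |Z2| < 1.96). The documents give no correlation, so a range is assumed:

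| Correlation | Chance of a false-positive primary result |
|---|---|
| 0 | 9.75% |
| 0.3 | 9.5% |
| 0.5 | 9.1% |
| 0.7 | 8.3% |
| 0.9 | 7.0% |

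**3. If both are required.** The chance that both are falsely significant is at most 5%. Joint power cannot exceed the GCS power. If GCS and MMN are each taken to have 80% (an assumption for MMN), joint power is 0.8 × 0.8 = 64% when independent. At correlations 0.3, 0.5, 0.7 and 0.9 the bivariate normal gives about 67%, 69%, 71% and 75%.

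**4. If GCS leads.** GCS is tested at the full 0.05 with about 67 evaluable per arm (75 × 0.9 = 67.5). Power = Φ(1.43/[SD × √(2/67)] − 1.960). This is Φ(2.834 − 1.960) = 81% with SD 2.920, and Φ(2.865 − 1.960) = 82% with SD 2.889. The planned 5% and 80% then hold for the primary conclusion.

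**5. If alpha is split equally (0.025 each, z = 2.241).** GCS power with 67 per arm is Φ(2.834 − 2.241) = 72%, or Φ(2.865 − 2.241) = 73%. To restore 80% for GCS would take 78 to 80 per arm. After attrition that is 87 to 89 per arm, or 174 to 178 in total against the planned 150.

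All power figures use the plan's own formula for means. They are not specific to the rank sum test.

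**The case against.** The strongest reply is that the sample size section attaches its 5% and 80% to GCS change only, and both reproduce. No section claims that 5% is a trial-wide error rate or that 80% is joint power. Calling GCS change the evaluation index also suggests that GCS leads. A success rule, a test order or an alpha split is often left to an analysis plan, and none is shown here.

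Much of this stands. The inflation is conditional on a rule that the article does not state, so a reader who infers that a stated property must be wrong whichever rule applies goes too far. If GCS leads, both figures hold.

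The appeal to an unseen plan carries less weight. The two primaries, the single 0.05 threshold and the sizing at the full 5% are all stated here. An equal alpha split added elsewhere would not fit the 150 patients (working, step 5).

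Other stronger readings are tempting but not supported:

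- **Four co-equal tests.** A reader might count GOS and Barthel as primaries because they precede the secondary list. The sentence naming the primaries ends with MMN, and the two scales carry no label. That is a gap to close, not evidence of equal rank.
- **Multiplicity within MMN.** Two electrode sites and four recordings might suggest many MMN tests. The article assigns MMN to a mixed model, one recording is the pre-treatment baseline, and how the sites enter the model is detail that an article may leave out.
- **64% as the joint power.** That is the independence case only. The Discussion links a rise in MMN amplitude to returning consciousness, which points to positive correlation and a higher figure.
- **A sized time point.** The sample size section says only before and after treatment. It does not say that the pilot change ran to the end of a 10-day course.

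**Conclusion.** The point holds as an unresolved success rule and should be fixed. It is not an error in the sample size. If either primary suffices, the false-positive chance for a primary result is about 7% to 10%, over assumed correlations from 0.9 down to 0. If both are needed, type I error is controlled at 5%, and joint power is about 64% to 75%, assuming 80% power for MMN and correlations from 0 to 0.9. The 5% and 80% are right for GCS change, and describe the trial's primary conclusion only if GCS is the lead outcome, which the outcome section does not say.

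**What to change.** Before unblinding, and recorded as a dated amendment, change the Abstract, Outcome measures and Statistical analysis in the same way:

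- State that GCS change from before to after treatment, the outcome already sized, is the single primary outcome. Alternatively, state that it is tested first at 0.05 and that MMN is tested at 0.05 only if GCS is significant.
- List GOS and Barthel as secondary. Their time origin needs reconciling in the same edit: the Abstract counts the 3 months from treatment and Outcome measures counts them from the trauma.

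The sample size stays at 150. Keeping two primaries with an equal alpha split would also settle the rule, but leaves GCS power near 73% or needs 174 to 178 patients. Requiring both would need power inputs for MMN that the article does not have.

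The cost is that an isolated positive MMN result can no longer be called a primary success. This is a substantive change of ranking, and it comes late: Trial status has recruitment running from June 2017 to June 2018. The Discussion says that those who collect and analyze the data learn the allocation only when the trial is complete, so the change can be made without sight of group results. The amendment should document this. If results by group have already been seen, the change must be reported as made after that.

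### ICU and hospital stay and expenses are defined without regard to death or withdrawal, so if mortality differs between arms a raw comparison can favour the arm with more deaths

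*Protocol article*

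**What the plan says.** The Outcome measures section lists the secondary outcomes: "Secondary measurements will be the length of stay in ICU and hospital, expenses in ICU and hospital", followed by the incidence of coma-related complications. Stay and expenses are thus four of the five. No qualifier for vital status is given, and mortality is not a named outcome.

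The Statistical analysis section has one general sentence that reaches stay and expenses: "Quantitative data will be presented as mean ± SD". It names tests for vital signs, complications and adverse events, the recovery scales and MMN. The rank-sum test is assigned to the scales: "Measurement of neural function recovery, including GCS, Glasgow Outcome Scale, and activities of daily living, will be analyzed using rank sum-test". No test is named for stay or expenses.

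Table 1 describes the population: "Initial GCS score less than 8 points on admission" and "Estimated ICU stay longer than 2 weeks". Very early deaths are excluded ("Vital signs are not stable on admission, die within 24 h"). Withdrawal criteria include "Life-threatening complications", secondary hydrocephalus, uncontrolled intracranial infection, re-operation and massive cerebral infarction. The article does not say whether the stay and cost data of withdrawn patients are analysed.

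The Background gives a mortality figure for TBI in China: "with the current mortality rate within the range of 2.7% to 21.8" percent.

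**The concern.** Length of stay and expenses are read as lower is better. A patient who dies in the ICU on day 5 has a shorter stay and probably a smaller bill than one who survives and leaves on day 30. Taken as plain quantities, the death is the better result. In a population admitted with a GCS below 8, some deaths after the first 24 hours are to be expected.

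The withdrawal criteria do not remove the difficulty. If withdrawn patients are kept, the short stays of those who die enter the mean. If they are dropped, the groups compared are no longer the groups randomised, because membership depends on complications that arose after allocation.

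At stake is a secondary claim that electro-acupuncture shortens the ICU stay or saves money, when the difference may come from deaths or from who was left in the analysis.

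**Working it through.** **The plan's own figures.** The article gives no expected stay, cost or trial-specific mortality, so there is no figure of its own to reproduce on this point. Its one calculated figure, 150 patients, rests on GCS change. With difference 3.70 − 2.27 = 1.43 and SD √((3.52² + 2.16²)/2) = 2.920, the formula gives 66 per arm, 132 in total, and 132/0.9 ≈ 147 after 10% attrition, close to 150. Nothing below depends on it except the arm size: 75 less 10% is about 67.

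**Scale of mortality.** Applying the Background range to 75 patients gives 0.027 × 75 = 2.0 and 0.218 × 75 = 16.4 deaths per arm. That range is for TBI in general, so this shows scale and is not a projection for the trial.

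**Shift in mean stay.** Let m be the proportion dying, S the mean stay of survivors and D the mean stay of those who die. Then mean stay = (1 − m)S + mD. If S and D are the same in both arms, the difference between arms is −(m₁ − m₀)(S − D). It is zero when m₁ = m₀.

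All values of S, D and m₁ − m₀ below are assumptions, apart from the two ends of the Background range:

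| S, D (days) | Mortality, arm 0 vs arm 1 | Mean stay (days) | Apparent gain for arm 1 (days) |
|---|---|---|---|
| 30, 10 | 10-point excess | n/a | 0.10 × 20 = 2.0 |
| 28, 7 | 10% vs 20% | 25.9 vs 23.8 | 2.1 |
| 28, 7 | 2.7% vs 21.8% | 27.4 vs 23.4 | 4.0 |
| 28, 10 | 10% vs 20% | 26.2 vs 24.4 | 1.8 |
| 21, 5 | 10% vs 20% | 19.4 vs 17.8 | 1.6 |
| 21, 5 | 15% vs 21.8% | 18.6 vs 17.5 | 1.1 |

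Expenses that accrue by the day move the same way.

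**How often this would mislead.** Simulation: 67 per arm, log-normal stays, survivors 28 days (SD 10), deaths 7 days (SD 3), identical in both arms, 2,000 trials per row, two-sided 5% tests. Entries are the share of trials in which arm 1 is significantly better; 2.5% is expected by chance.

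| Mortality, arm 0 vs arm 1 | t-test, raw stay | Rank-sum, raw stay | Rank-sum, deaths ranked worst |
|---|---|---|---|
| 10% vs 10% | 2.5% | 2.5% | 3.1% |
| 10% vs 20% | 16.1% | 14.8% | 0.1% |
| 2.7% vs 21.8% | 52.7% | 46.9% | 0.0% |

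The simulation standard error at 2.5% is √(0.025 × 0.975/2000) ≈ 0.35 points, so 3.1% is compatible with 2.5%. At 10% vs 20%, the arm with more deaths has the shorter raw mean in 84% of trials. Moving to a rank-sum test on raw stay barely helps; the place given to deaths is what matters.

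**If patients who die are dropped.** In this set-up both arms then average 28 days and the shift vanishes. That happens only because survivors were assumed identical between arms. Table 1 also withdraws patients for reasons that need not end in death, and their stays may be unusual. The direction of the resulting selection cannot be determined from the article.

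**The case against.** The strongest reply is that the article commits to no faulty analysis. No test is stated for stay or expenses, the mean-and-SD sentence is a general descriptive one, and the handling of deaths in resource-use outcomes is often settled in a full protocol or analysis plan that is not shown here. This stands as far as it goes. A reader might infer that the plan prescribes a raw test, or that it counts early deaths as short, cheap stays. The text says neither. What remains is the outcome definition itself, which the article does fix: stay and expenses regardless of vital status, with mortality not named beside them.

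Second, Table 1 may take many dying patients out, through the exclusions (death within 24 hours, unstable vital signs, families with weak treatment intent) or through withdrawal. That also stands, and it limits the first mechanism. It puts selection after randomisation in its place, and the article does not say which applies.

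Third, the shift needs a mortality difference, and nothing in the article predicts one. True: at equal mortality the false-favourable rate stays at 2.5%.

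Fourth, stay would not be read alone, since adverse events and the 3-month Glasgow Outcome Scale are also compared, and total expense including deaths is a legitimate resource-use quantity. Both points are fair. They support keeping raw expenses as a description, but they do not make a lower figure in the arm with more deaths a benefit.

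**Conclusion.** The point holds in a limited form. As defined, four of the five secondary outcomes can favour the arm with more deaths if mortality differs and those patients are analysed. If they are dropped under the withdrawal criteria, the comparison is selected on post-randomisation events. Under the assumed stays and mortality gaps of 6.8 to 19.1 points, the apparent gain is about 1.1 to 4.0 days, and about 2 days for a 10-point gap.

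A reader might go further and take 2 to 16 deaths per arm as a forecast, or conclude that the trial's stay results will be biased. The documents do not support that: the mortality range is a general one, the stays are assumed, and no mortality difference is anticipated. The primary outcomes and the sample size are unaffected. The change is worth making for the secondary outcomes and is not critical to the trial.

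**What to change.** For ICU stay and for hospital stay, analyse all randomised patients, including those withdrawn under Table 1. Give patients who die in that setting the worst rank, tied, and compare the arms by rank-sum test. Report raw stay and raw expenses by arm, separately for survivors and for patients who died, as descriptive results. Show mortality by arm beside every stay and expense comparison.

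ICU-free or hospital-free days are an alternative only if the necessary dates are already collected. The article does not show that readmission dates are recorded after discharge. A 3-month window would also need one starting point: the Abstract counts from treatment and the Outcome measures section from trauma.

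Cost: a change to derivation and reporting, with no added visits. It needs stay and death status for every randomised patient, and the article does not state that these are kept for withdrawn patients, so this should be confirmed. The small downside is that a ranked composite is less familiar than raw length of stay and does not give a difference in days.
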